#### Primary outcomes

The primary outcomes are activity performance and satisfaction with activity performance, which will be assessed by the COPM. The COPM measures a client’s self-perception of activity performance within nine activity areas; personal care, functional mobility, community management (self-care), paid/unpaid work, household management, play/school (productivity), and quiet recreation, active recreation, and socialization (leisure) [14]. The COPM starts with a semi-structured interview during which participants describe the activities that they consider to be important, but difficult to perform. Each activity is entered in one of the nine COPM activity categories and the importance of each activity is rated on a 10-point scale (10 = very important). The participant is then asked to choose up to five of the most important activities and to rate their performance and satisfaction with the performance of each activity on a scale from 1–10 (where a higher score reflects better performance and higher satisfaction). According to the COPM manual, a change of two points indicates a clinically relevant improvement or deterioration [14]. The Norwegian version of the COPM has been tested in terms of its psychometric properties with good results [15, 16].

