**Methods/Design:**

The study is a multicenter controlled trial. In total, 44 Norwegian municipalities will participate, including eight municipalities as a control group. For three municipalities with two zones, one will be assigned to the control group and the other to the intervention group. The experimental group will be offered reablement and the control group standard treatment. The sample will comprise approximately 750 participants. People will be eligible if they are home-dwelling adults, understand Norwegian, and have functional decline. Participants will be assessed at baseline, and after 10 weeks, 6 months, and 12 months. The primary outcome will be activity and participation measured by the Canadian Occupational Performance Measure. Physical functioning will be measured by the Short Physical Performance Battery and health-related quality of life by the European Quality of Life Scale. Coping will be measured by the Sense of Coherence questionnaire and mental health by the Mental Health Continuum Short Form. Costs will be generated based on registered working hours in different professions. Data analyses will be performed according to intention to treat. Univariate analysis of covariance will be used to investigate differences between the groups at baseline and the end of intervention. The data will be organized into two levels using a multilevel structure, i.e., individuals and municipalities, which will be analyzed using linear mixed-effects models. The working hours data (panel data) will be analyzed with random mixed-effects regression models. The cost-effectiveness of reablement will be evaluated according to the incremental cost-effectiveness ratio and uncertainty will be explored via the bootstrap method.

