### Outcomes

Reablement is based on a holistic approach, so different outcomes will be used to detect potential changes in a variety of outcomes, including mental health and coping as a sense of coherence. The outcomes will also include cost outcomes such as consumption of various home-based services. These outcomes will be registered on a weekly basis during the first 6 months after inclusion. Table 2 provides an overview of the different outcomes that will be measured.

**Table 2 Tab2:** Summary of measures to be collected

Outcome	Data collection instrument and scale	Time points
Primary outcome measures		
Activity performance	Canadian Occupational Performance Measure. Scale 1–10, 1 is low performance	t1, t2, t3, t4
Satisfaction with activity performance	Canadian Occupational Performance Measure. Scale 1–10, 1 is low satisfaction	t1, t2, t3, t4
Secondary outcome measures		
Physical Performance Test	Short Physical Performance Battery, which has three parts: 1) standing balance, 2) walking four meters at regular pace, and 3) ability to stand up and sit rapidly five times. Each part is scored from 0–4 points and the total score = 0–12 points, where 0 is low performance	t1, t2, t3, t4
Health-related quality of life	European Quality of Life Scale (EQ-5D), which comprises the EQ-5D index and the EQ-5D visual analog scale (VAS). The EQ-5D index has five domains (mobility, self-care, activities, pain/discomfort, and anxiety/depression) on a five-point scale ranging from no problems to being unable. The EQ-5D VAS measures total health status on a scale 1–100 where 100 is high	t1, t2, t3, t4
Sense of coherence	Sense of Coherence Questionnaire (SOC-13). Total score ranging from 13 to 91, where higher scores indicate better sense of coherence. Responses are measured on a seven-point Likert scale (1–7)	t1, t2, t3, t4
Positive mental health	The Mental Health Continuum Short Form (MHC-SF). The MHC-SF comprises 14 items, which are scored on a six-point scale (0–5). The summary score ranges from 0 to 70, where higher scores indicate higher levels of positive mental health	t1, t2, t3, t4
Other measures		
Age	Years	t1
Gender	Female/Male	t1
Marital status	Married/Cohabiting/Single/Widowed/Separated or divorced	t1
Living situation	Living alone/Living together with someone	t1
Level of education	Primary school/High school/1–3 years University/>4 years University	t1
Current work status	Retired/Disability benefit/Working/Sick leave/Unpaid work/Unemployed/Student	t1

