### Sample size calculation

In an earlier study performed with older adults, the standard deviation for the primary outcome was shown to be 1.4 for COPM performance and 1.6 for COPM satisfaction [33]. The current trial is a multicenter study with 44 participating municipalities, so we expect that the variation in the COPM scores will be larger, and thus we employ a conservative estimate of 2.5 for the standard deviation. Furthermore, the allocation of participants to the intervention group or control group will not be randomized, and the number of participants in the intervention group will probably be three to four times that in the control group. We aim to detect a change of one point as statistically significant at a two-sided 5 % level and with a power of 80 %. Based on these estimates, sample size calculations indicate that we need to include 70 participants in the control group and 260 in the intervention group. Therefore, to consider the possibility of a relatively high dropout rate (up to 35 %) due to frail participants, a minimum of 107 and 400 participants will be included in the control and intervention groups, respectively.

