### Participants

The analysis will include all participants who answer the questionnaire both at baseline and follow-up, even if they drop out of the intervention (intention-to-treat analysis). *P*-values will be two-sided and significant at *P* ≤ 0.05.

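### Two COPM scores are both primary and each is tested at 0.05, with no ranking, primary time point or success rule; if either score at the end of intervention counts, the nominal false-positive rate is about 7–10%

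*Protocol article*

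**What the plan says.** - **Two primary outcomes.** Protocol article, Primary outcomes: "The primary outcomes are activity performance and satisfaction with activity performance, which will be assessed by the COPM". Table 2 lists both under primary outcome measures with the same schedule: "Canadian Occupational Performance Measure. Scale 1–10, 1 is low performance t1, t2, t3, t4" and "Canadian Occupational Performance Measure. Scale 1–10, 1 is low satisfaction t1, t2, t3, t4". That gives each score three follow-ups: 10 weeks, 6 months and 12 months.
- **One threshold.** Statistical analysis, Participants: P-"values will be two-sided and significant at" 0.05 or below. No adjustment is mentioned.
- **One comparison in the sample size.** Sample size calculation: "We aim to detect a change of one point as statistically significant at a two-sided 5 % level and with a power of 80" %. The paragraph cites earlier SDs for both scores (1.4 and 1.6) and then uses a single value: "we employ a conservative estimate of 2.5 for the standard deviation". It does not say which score or visit the calculation is for.
- **Closest candidate for a primary contrast.** The abstract (Methods/Design) and Descriptive statistics both plan an analysis of covariance of group differences at baseline and at the end of intervention. Neither calls it primary. Analysis of effectiveness describes mixed models without naming a time point or a single test of the group effect.
- **Singular wording.** The abstract says: "The primary outcome will be activity and participation measured by the Canadian Occupational Performance Measure". The Discussion also speaks of one primary outcome, the COPM.

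**The concern.** The article fixes three things that do not fit together: two primary scores, a 0.05 threshold for each P-value, and a sample size that spends the full 5% on one comparison. With two chances to succeed and no ordering, the probability that at least one primary test is significant when reablement has no effect exceeds 5%. The gap also leaves the main conclusion open. If performance is significant and satisfaction is not, or if the 10-week result and a later one differ, the article does not say whether the trial has met its primary objective. That choice would then be made with the results in view.

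**Working it through.** **1. Inputs from the article.** Two primary scores and three follow-ups each (Primary outcomes, Table 2); two-sided 0.05 per test (Participants); difference 1 point, SD 2.5, power 80%, 70 control and 260 intervention (Sample size calculation). The article gives no correlation between the scores or between visits, so 0 to 0.9 is assumed and the range is shown.

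**2. The plan's own sample size.** With ratio k = 260/70 = 3.71,

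n(control) = (1 + 1/k) × (1.960 + 0.842)² × 2.5² / 1² = 1.269 × 7.85 × 6.25 ≈ 62.3, so 63 control and 234 intervention.

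The stated 70 and 260 are somewhat larger, and so conservative. Their standard error is 2.5 × √(1/70 + 1/260) = 0.337, so power is Φ(1/0.337 − 1.960) = Φ(1.01) = 84.4%. This confirms that the figure is for one test at the full 5%; there is no allowance for a second score. It takes participants as independent.

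**3. Two scores at one time point, either counts.** The rate is 1 − P(|Z1| ≤ 1.96 and |Z2| ≤ 1.96), from simulated correlated normal test statistics (2,000,000 draws):

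| Between-score correlation | False-positive rate |
|---|---|
| 0 (exact: 1 − 0.95²) | 9.75% |
| 0.5 | 9.1% |
| 0.7 | 8.3% |
| 0.9 | 7.1% |

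**4. Two scores at three follow-ups, any counts.** Same method (1,000,000 draws), with a common correlation between visits:

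| Between-score / between-visit correlation | False-positive rate |
|---|---|
| 0 / 0 (exact: 1 − 0.95⁶) | 26.5% |
| 0.5 / 0.5 | 21.9% |
| 0.7 / 0.7 | 17.8% |
| 0.9 / 0.9 | 11.5% |

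**5. Both scores required at one time point.** A false claim needs both tests to reject, so the rate cannot exceed that of either test alone, 5%.

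**6. What each remedy costs in power at 70/260, on the plan's inputs.**
- Fixed sequence: the first test keeps the full 5%, so power is 84.4%.
- Both required: if each score truly differs by 1 point with SD 2.5, power lies between 0.844 × 0.844 = 71.2% (independent scores) and 84.4% (perfectly correlated).
- Splitting alpha, 0.025 per score: 76.7%; restoring 80% needs 76 + 283, or 117 + 436 after 35% dropout.
- Bonferroni over six tests: 63.0%; restoring 80% needs 97 + 361, or 150 + 556 after dropout.

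**The case against.** The strongest reply is that this is a journal article, and multiplicity rules are commonly left to an analysis plan that is not shown. That stands as far as the missing adjustment goes: an unseen plan may contain one. It does not dispose of the point, because the article itself names two primary outcomes, sets the threshold and sizes one comparison, and those statements do not agree. It is also true that the article never claims familywise control at 5%; its 5% is a per-test level.

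A reader might infer that the plan lets any of six tests carry the primary claim, and so that the error rate is 17% to 26%. The documents do not support that as a fact. Table 2 says when the scores are collected, not which tests are confirmatory. The end-of-intervention analysis of covariance, with rehabilitation capped at 10 weeks (Table 1), points to t2, which leaves two tests. A mixed model over time need not yield three separate tests per score. Independence is also implausible, since the same person rates the same chosen activities on both scales.

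It may also be said that the research question pairs performance with satisfaction, which could mean that both must succeed. That is possible, but no section says so.

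Finally, a reader might see a contradiction between the singular primary outcome in the abstract and the two in the body. This is better read as loose wording: the COPM is one instrument with two scores, and the Discussion uses the singular too.

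**Conclusion.** The concern holds in a conditional form. The article does not settle which COPM score, at which visit, under which success rule, decides the trial, while testing each at 0.05 and sizing for one.

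- End of intervention taken as primary, either score sufficient: nominal false-positive rate about 7–10%.
- Any follow-up also sufficient: about 12–26%, an upper scenario that the article does not state as its rule.
- Both scores required at one time point: no inflation.

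The first two ranges rest on assumed correlations from 0.9 to 0; both exceed 5% throughout. They are nominal rates, computed as if the tests were otherwise valid. Allocation is not randomised (zones were assigned by the municipality on practical grounds) and participants are nested in municipalities, so confounding and clustering affect the real error rate separately. The point should be corrected because it bears on the main effectiveness claim, but it does not undermine the design.

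**What to change.** Name 10 weeks (t2) as the primary time point. Test in fixed sequence at two-sided 5%: COPM performance first, and COPM satisfaction only if performance is significant. Performance comes first in the research question, Table 2 and the Primary outcomes section, so this order follows the article's own, but it is a choice rather than something the article prescribes. Requiring both scores to succeed at 10 weeks is an acceptable alternative.

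Report the 6- and 12-month COPM contrasts as secondary, with confidence intervals. Align the abstract, Table 2 and the sample size paragraph, and state there which score and visit the one-point difference refers to. Make and date the change before any group comparison is seen.

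**Cost.** The fixed sequence needs no extra participants. Satisfaction cannot be claimed as a confirmatory result if performance fails, and the later visits lose the primary status that Table 2 gives them, so this changes the endpoint definition and is more than an edit of wording. Requiring both scores instead costs some power (71% to 84% at 70/260, against 84% for one score). Neither option addresses confounding from non-randomised allocation or clustering within municipalities.

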#### Secondary outcomes

The study will include several secondary outcomes. Physical functioning will be measured by the Short Physical Performance Battery (SPPB). The SPPB aims to identify people at risk of functional decline, and it is a screening test for balance, walk function, and muscle strength in the lower limbs [17]. The SPPB comprises: 1) standing balance including side-by-side standing, and semi-tandem and tandem standing; 2) a walking test for four meters at regular pace; and 3) standing up and sitting down rapidly five times. For each component, the time required is recorded and converted into points (0–4), thereby giving a total score of 0–12 points. Freiberger et al. [18] conducted a systematic review and demonstrated that the SPPB has good validity, reliability, and responsiveness.

HRQoL will be measured by the European Quality of Life Scale with five dimensions (EQ-5D). EQ-5D comprises a questionnaire and a visual analog scale (VAS). The EQ-5D questionnaire has five domains (mobility, self-care, activities, pain/discomfort, and anxiety/depression) with five levels (no problems to extreme problems) [19]. According to the responses to all five dimensions, the HRQoL is calculated based on the UK tariff. The VAS scale is an indication of how individuals value their own health on a scale of 0–100.

The EQ-5D will be employed to measure quality-adjusted life-years (QALYs) for the cost-effectiveness analysis. QALYs are estimated by combining HRQoL with time and they are reported on a scale of 0–1, where 0 indicates death and 1 denotes perfect health. The EQ-5D has been translated into Norwegian, with satisfactory reliability, validity, and responsiveness among elderly people [20].

Coping will be measured using the Sense of Coherence (SOC) questionnaire. SOC-13 was developed by Antonovsky [21]. SOC-13 is self-reported and it comprises 13 items related to comprehensibility (five items), manageability (four items), and meaning (four items). The responses to all items are scored on a seven-point Likert-type scale. The total score ranges from 13 to 91, where higher scores indicate a stronger sense of coherence. SOC-13 has been tested for validity and reliability in several studies [22–26]. A systematic review concluded that the SOC scale appears to be a reliable, valid, and cross-culturally applicable instrument for measuring how people manage stress and stay well [23].

The Mental Health Continuum Short Form (MHC-SF) is designed to measure three dimensions of the positive mental health concept: emotional well-being (EWB), psychological well-being (PWB), and social well-being (SWB) [27, 28]. The MHC-SF comprises 14 items and the possible score range is 0–70. Each item is scored by rating the frequency of different feelings during the past month on a six-point scale, ranging from never (0) to every day (5). Higher scores indicate higher levels of positive mental health [27, 28]. Previous studies support the three-factor structure of the MHC-SF [29–31]. Convergent validity has been found in the subscales, which correlate well with the corresponding aspects of well-being and functioning [30], and with the scale as a whole [29]. A previous study demonstrated the high internal reliability of the whole scale as well as the EWB and PWB subscales, the adequate internal reliability of the SWB subscale, and moderate test–retest reliability [30]. The MHC-SF has been translated into Norwegian and employed successfully as a whole scale in a sample of Norwegian psoriasis patients [32].

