## Methods/design

### Design and setting

This will be a large multicenter clinical controlled trial. The study will be conducted in primary care settings in 44 of the 428 Norwegian municipalities, including eight municipalities that function as a control group; for three municipalities with two zones, one will be assigned to the control group and the other to the intervention group (see Fig. 1 for flow diagram). The allocation of zones to the intervention or control group was based on practical reasons and decided by the municipality. The municipalities included represent 17 % of the total population in Norway. The experimental group will be offered reablement and the control group standard treatment. The sample will comprise approximately 750 participants, who will be assessed at baseline and after 10 weeks, 6 months, and 12 months.

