### Analysis of cost-effectiveness

To assess the cost-effectiveness of reablement, we will need to estimate health outcomes and costs. The health outcomes will be measured using the EQ-5D and the costs will include health care sector costs. To estimate costs, we will include the cost of the intervention, which includes the hours, frequency, and type of training received in private homes according to health care professionals. Furthermore, the use of other health care services (home care services, rehabilitation, and institution) will be recorded for both the intervention and control groups over a period of 6 months. Standard methods for economic evaluation will be applied and the cost-effectiveness will be calculated as the incremental cost-effectiveness ratio, which is defined by the cost per incremental QALY. Further uncertainty will be determined by applying the bootstrap method with 1000 replicates to illustrate the variation in the patient population in terms of incremental health gains and costs.

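### The responder-only analysis set excludes people who die before answering the required follow-up, so the QALY value of 0 for death cannot enter the ICER for them

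*Protocol article*

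**What the plan says.** All references are to the protocol article.

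- **Secondary outcomes:** "The EQ-5D will be employed to measure quality-adjusted life-years (QALYs) for the cost-effectiveness analysis". QALYs combine quality of life with time, and "they are reported on a scale of 0–1, where 0 indicates death and 1 denotes perfect health".
- **Participants (under the statistical analysis):** "The analysis will include all participants who answer the questionnaire both at baseline and follow-up". Stopping the intervention does not remove a person, and the section calls this an intention-to-treat analysis.
- **Analysis of cost-effectiveness:** "The health outcomes will be measured using the EQ-5D and the costs will include health care sector costs". The result is an "incremental cost-effectiveness ratio, which is defined by the cost per incremental QALY". No separate analysis set is named. Service use is recorded for 6 months.
- **Design and setting:** the participants are those "who will be assessed at baseline and after 10 weeks, 6 months, and 12 months", so there are three follow-ups. The Participants section does not say which of them a person must answer.
- **Sample size calculation:** the plan allows for "a relatively high dropout rate (up to 35 %) due to frail participants", and states that allocation is not randomised.

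**The concern.** Death is not an unknown outcome on the QALY scale, because the article gives it a value. The inclusion rule depends on answering a questionnaire, which someone who has died cannot do. If that rule governs the economic analysis, the people with the largest QALY loss are left out, although the set is labelled intention-to-treat.

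Cost-effectiveness is one of the four research questions, and the QALY is the health outcome in the ICER. Municipalities and zones were not randomised to arms, so equal mortality cannot be presumed. If deaths differ between arms, leaving them out changes the ICER denominator, and the direction depends on which arm has more deaths.

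**Working it through.** **1. Who is excluded.** The text allows more than one reading of follow-up:

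| Meaning of follow-up | Deaths outside the set |
|---|---|
| Any one of the three | Deaths before the first answered follow-up |
| Every one, or the last | All deaths before the 12-month assessment |

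Some deaths are excluded under each reading. A person who answers at 10 weeks and dies later stays in the set under the first reading, and could be scored 0 from death.

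**2. The plan's own figure.** The only stated figure that bears on this is the dropout allowance in the sample size section: 70/0.65 = 107.7 (stated 107) and 260/0.65 = 400 (stated 400). It reproduces within rounding. The plan thus allows for 107 − 70 = 37 control and 400 − 260 = 140 intervention participants without follow-up. These are upper limits on all losses and do not count deaths.

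**3. Size if all deaths are excluded.** Assumptions, none from the document: mean utility u of 0.5 to 0.7, the same in both arms and the same before death; share m dying within a window of T years; deaths evenly spread over the window.

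- Mean QALY with deaths scored 0: u × T × (1 − m/2)
- Mean QALY with deaths dropped: u × T
- Shift in the between-arm difference: (u × T/2) × mortality difference

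For a 5-point mortality difference within the window:

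- 12 months: 0.5/2 × 0.05 = 0.0125, up to 0.7/2 × 0.05 = 0.0175
- 6 months: half of this, 0.00625 to 0.00875

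If the 5 points build up evenly over 12 months, only 2.5 fall in the first 6 months. At u = 0.6 the 6-month shift is then 0.6 × 0.5/2 × 0.025 = 0.00375.

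**4. Size if any one follow-up suffices.** Suppose everyone alive answers at 10 weeks. Then only deaths in the first 10 of 52 weeks are lost, and each occurs at week 5 on average. To first order, the 12-month shift is u × 0.05 × (10/52) × (47/52), which is 0.0043 to 0.0061 for u = 0.5 to 0.7.

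**5. Scale.** With an assumed QALY SD of 0.20 and the planned evaluable numbers, the standard error of the difference is 0.20 × √(1/70 + 1/260) = 0.027. The 12-month shift in step 3 is therefore 0.0125/0.027 to 0.0175/0.027, about 0.46 to 0.65 of a standard error.

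**6. Direction.** Assume utility 0.60 in control and 0.63 in intervention, with all deaths excluded. For 5% control and 8% intervention mortality over 12 months, the difference including deaths is 0.63 × 0.96 − 0.60 × 0.975 = 0.0198. Without deaths it is 0.03, a ratio of 1.52. The same formula gives:

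| Mortality, control / intervention | Incremental QALY, deaths dropped ÷ deaths included |
|---|---|
| 5% / 5% | 1.03 |
| 5% / 3% | 0.84 |
| 10% / 5% | 0.68 |
| 5% / 8% | 1.52 |
| 5% / 10% | 2.22 |

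**The case against.** The case against has real force.

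- **A reader might infer that no death is ever scored 0 and that the ICER rests wholly on survivors.** The article does not support this. It leaves open which follow-up is required, and on the widest reading later deaths stay in the set.
- **A reader might infer that people who die add cost to the ICER but no QALY loss, because home-visit minutes are registered without a questionnaire.** This does not hold either. If the responder rule governs the ICER, it removes their costs too. If it does not, the QALY exclusion falls away as well. No section gives costs a wider set.
- **Scoring detail may sit in an analysis plan that is not shown.** That is fair, and the absence of a scoring rule is not the point here. The value of 0 for death is correct in itself, and the cost-effectiveness section promises standard methods. What remains is a stated inclusion rule, with no exception for the economic analysis, that conflicts with the QALY scale and the intention-to-treat label. An analysis plan that followed it would carry the problem forward.
- **This is only one consequence of a completer set.** It has the same source, but the remedy differs. Imputation suits living non-responders, whereas a death has a known value. The article proposes no imputation of QALYs, so it cannot be faulted for imputing the dead.
- **The size is assumed.** This stands. The eligibility criteria also exclude people who are terminally ill or need nursing home placement, which lowers expected mortality without removing it. With equal mortality the effect is small.

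**Conclusion.** The point holds in limited form. Under the only analysis set the article states, people who die before answering the required follow-up are excluded, and their value of 0 cannot enter the ICER. How many deaths this affects depends on a definition of follow-up that the article does not give.

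The bias is material only if mortality differs between arms, and it can go either way. For a 5-point difference over 12 months, the illustrative shift is 0.0125 to 0.0175 QALY if all deaths are lost, and about 0.004 to 0.006 if only deaths in the first 10 weeks are lost. Over 6 months, the first range halves for the same mortality difference within the window. Every mortality, utility, SD and gain figure behind these results is an assumption. The finding concerns the cost-effectiveness question and leaves the COPM primary outcomes aside. It should be corrected because the rule works against the plan's own QALY scale and the correction is cheap.

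**What to change.** In the Analysis of cost-effectiveness section:

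1. Exempt this analysis from the responder rule in the Participants section, and define its set as all enrolled participants.
2. Assign utility 0 from the date of death to the end of the QALY period. Count costs up to death and set them to 0 afterwards.
3. Impute only for living non-responders.
4. Use the same participants and the same time window for costs and QALYs in each bootstrap replicate. EQ-5D runs to 12 months and service-use recording for the economic analysis to 6 months, so the window has to be stated.

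The cost is a few sentences of text, plus dates of death obtained through the municipal contact persons who already handle data collection. The standard error of the QALY difference becomes slightly larger. No extra visits are needed.
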